### The intervention

The digital intervention (“Hypertension Plus”) was provided by Omron Healthcare combining blood pressure telemonitoring with prompts for hypertension management including medication titration intended to facilitate remote care [4]. The intervention is based on workflow algorithms developed from research data and decision support tools designed to be compliant with National Institute for Health and Care Excellence (NICE) guidelines [8].

The system combines a web-based dashboard for professionals, which both reads and writes data to the practice clinical system, with a mobile phone “app” which is downloaded by participating patients and used to upload BP readings. Patients are invited to use the digital intervention via contact from their practice and then sign up via a bespoke web interface. The choice of which patients receive an invitation is at the discretion of practices, but they are typically people with raised BP receiving antihypertensive treatment plus some without a diagnosis of hypertension. Telephone and online support is provided for those people having problems accessing or engaging with the technological platforms.

The digital intervention is a commercial system and is licenced annually, usually at local healthcare organisation level (known as primary care networks (PCN) or Integrated Care Boards in England). Implementation is being led by Omron working with the National Association for Primary Care (NAPC, https://napc.co.uk) and includes training for practices, support with identification of appropriate groups, support for patients, and peer led support facilitated by the NAPC.

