### Quantitative study

Pseudonymised coded and numeric clinical data will be extracted using the Oxford-Royal College of General Practitioners Clinical Informatics Digital Hub (ORCHID) system [7]. ORCHID is a secure system that regularly extracts pseudonymised data from member practices for disease surveillance, quality improvement and research purposes (https://orchid.phc.ox.ac.uk/index.php/orchid-data/). Data will not be extracted from records of patients who have opted out of use of their health records in research. The analysis will take place within the ORCHID trusted research environment. Outside of ethically approved trials with individual consent, no individual data leaves this network. All aggregate data extracts subject to statistical disclosure control.

People invited to use the digital intervention will be compared to patients on the practice hypertension register who have not been invited. Outcomes will be assessed using predefined curated variables of Systematised Nomenclature of Medicine (SNOMED) clinical terms (CT) codes (Fig. 1; see https://github.com/[name] for codelists) [9].

(Fig. 1)

The most recent routinely collected retrospective data extracted at baseline will include:

Age (years).Sex.Ethnicity.Smoking status.Index of Multiple Deprivation (IMD), a measure of socioeconomic status.Height, weight, body mass index (kg/m2).Total and HDL cholesterol (mmol/L).Systolic and diastolic blood pressure (clinic and/or home readings).Pulse.Past medical history:Diagnosis of diabetes (Type 1 or 2).Previous myocardial infarction or stroke.Diagnosis of chronic kidney disease.Medication useStatin treatment (drug type and dose).Antihypertensive medication use.Other current cardiovascular medication.Electronic Frailty Index (eFI) and/or characteristics required to calculate this.Health Economic Resource use: relevant consultations, referrals and admissions as available.Practice identifier (pseudonymised).

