### Outcomes

### Primary outcome

The primary outcome will be change in systolic blood pressure (SBP, clinic and home BP both included) in mmHg extracted from the electronic healthcare record comparing 12 months before and after intervention implementation along with comparison between those on the hypertension register invited to use and not invited to use the intervention.

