### Sample size

Sample size requirements for this study were determined through simulation. A mean BP of 148 mm Hg was assumed, with practice variation (standard deviation, SD) of 5 mm Hg. Within a practice, patient variation (SD) was assumed as 17 mm Hg and measurements within a patient were assumed to vary by 10 mm Hg (SD) about the patient mean. Effect size was assumed to be -3 mm Hg (BP 3 mm Hg lower in patients using the digital intervention) and a minimum of 4 BP measurements for each patient. This demonstrated that to achieve 90% power at the 5% significance level, 100 patients each drawn from 8 general practices would be required for this study (800 patients in total, 91% power). Assuming greater variation (practice SD = 10 mm Hg, patient SD = 22 mm Hg or measurement SD = 14 mm Hg), the required sample size was 100 patients from 14 practices respectively. The available sample will depend upon the implementation rate as well as recruitment and will include as many patient records as are available.

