### Statistical analysis

Descriptive statistics will be presented as the means and standard deviation (SD), proportions, and medians with interquartile ranges where appropriate. In the efficacy analyses for blood pressure, mixed-effects model repeated measures will be used to compare the changes in BP for people on the hypertension registers (i.e. with a clinical code for hypertension) between one year before and one year after implementation of the digital intervention within each practice. Fixed effects in the model are the exposure, whether BPs are measured (home or clinic), periods (12 months before and after implementation), interaction terms between the exposure and time period variable and covariates that were selected a priori because they have been reported to show correlations with both BP and cardiovascular (CVD) risk and could potentially confound the association between BP and CVD risk. These potential confounders will include baseline demographic characteristics (age, sex, ethnicity, IMD and frailty), clinical characteristics at baseline (SBP and DBP, total cholesterol, smoking, antihypertensive medication use), past history (diabetes, established cardiovascular disease, and chronic kidney disease). Random effects for patient and practice level average BP will also be included in the model. These covariates were selected a priori because they have been reported to show correlations with both BP and CVD risk and could potentially confound the association between BP and CVD risk [12]. Covariates are defined using the closest available electronic healthcare records data prior to baseline. The intervention analysis will take a similar approach albeit limited to the self-monitoring group and the variables included in the Hypertension-Plus dataset.

A 5% significance level will be used for all analyses/ tests.

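### The primary contrast is a change, but the model's named random effects cover only average BP; if patients differ in true change, its confidence interval will be too narrow

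*Protocol article*

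**What the plan says.** Under Primary outcome, the protocol article defines the outcome as change in systolic BP and gives the contrast as: "comparing 12 months before and after intervention implementation along with comparison between those on the hypertension register invited to use and not invited". Under Quantitative study, exposure is set at patient level within practices: "People invited to use the digital intervention will be compared to patients on the practice hypertension register who have not been invited".

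Under Statistical analysis, "mixed-effects model repeated measures will be used to compare the changes in BP for people on the hypertension registers". Exposure, period and "interaction terms between the exposure and time period variable" are fixed effects. The random part is given in one sentence: "Random effects for patient and practice level average BP will also be included in the model". That section names no random period effect, no random exposure-by-period effect, no residual covariance and no robust standard error.

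Under Sample size, the variance inputs are all for BP level or single readings. For practices: "A mean BP of 148 mm Hg was assumed, with practice variation (standard deviation, SD) of 5 mm Hg". For patients, and for single readings around each person's own average, the text is: "patient variation (SD) was assumed as 17 mm Hg and measurements within a patient were assumed to vary by 10 mm Hg (SD) about the". No SD is given for change or for variation of the effect between practices. At least four readings per patient are assumed.

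**The concern.** A random intercept lets patients and practices differ in BP level. It does not let them differ in how far BP moves from one year to the next, and that movement is the primary target. All of a patient's readings in the second year share that patient's own change. With intercepts only and independent residuals, the model counts each extra reading as nearly independent evidence about change.

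Variation in change is to be expected. The intervention prompts individual medication titration, and the Background names clinical inertia and adherence as the obstacles it addresses. Clinic and home readings both count and patients upload readings through an app, so invited patients may well have more readings after implementation.

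At stake are the type I error and the confidence interval of the primary comparison.

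**Working it through.** **1. The plan's own figure.** The article states 91% power for a 3 mm Hg effect with 800 patients (8 practices of 100). The design behind it is not defined. I take a two-sided 5% test and power = Φ(3/SE − 1.96). The practice level cancels because exposure varies within practice.

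- Post-period comparison, four readings: variance per patient 17² + 10²/4 = 314. For 400 v 400, SE = √(314 × 2/400) = 1.25, power 67%. For 800 v 800, 92%, but that is not 800 in total.
- Difference in changes, 400 v 400, variance of a patient's change 10²/a + 10²/b for a readings before and b after: SE 0.71, power 99% (2+2); SE 0.82, 96% (1+3); SE 1.00, 85% (1+1).

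None of these 800-patient calculations gives 91%. With 2+2 readings, 91% would need about 19% of the 800 to be invited, a share the article does not state. So the figure cannot show whether variation in change was allowed for.

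**2. Patient variation in change.** From the article: measurement SD s = 10. Assumed: 400 v 400 patients, m readings in each period, true change varying between patients with SD τ.

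- True variance of a patient's observed change: 2s²/m + τ².
- Variance the random-intercept model reports: (2/m) × [s² + (mτ²/2)/(2m − 1)].
- SE of the interaction: √(variance × 2/400). Coverage: 2Φ(1.96 × model SE/true SE) − 1.

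Example, m = 2, τ = 5: true variance 100 + 25 = 125, SE 0.79; model variance 100 + 25/3 = 108.3, SE 0.74; coverage 93%.

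| Readings before + after | τ (mm Hg) | Model SE | True SE | Coverage |
|---|---|---|---|---|
| 1+1 | 5 or 10 | 1.06 or 1.22 | 1.06 or 1.22 | 95% |
| 2+2 | 0 | 0.71 | 0.71 | 95% |
| 2+2 | 5 | 0.74 | 0.79 | 93% |
| 2+2 | 10 | 0.82 | 1.00 | 89% |
| 4+4 | 5 | 0.52 | 0.61 | 90% |
| 4+4 | 10 | 0.57 | 0.87 | 80% |

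Simulation with 8 practices of 50 v 50 patients (3,000 runs per setting) gave 93% and 89% for 2+2, and 90% and 81% for 4+4.

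**3. Unequal reading counts.** Suppose everyone has 3 readings before, and after implementation non-invited patients have 3 and invited patients 15. This pattern is an assumption.

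- Sampling part: (10²/400) × (1/3 + 1/3 + 1/3 + 1/15) = 0.267.
- True variance: 0.267 + 2τ²/400.
- Model residual variance: 100 + τ² × (1.5 + 2.5)/(5 + 17). Here 1.5 = 3×3/6 and 2.5 = 3×15/18; 5 and 17 are the within-patient degrees of freedom.
- τ = 5: model SE 0.53, true 0.63, coverage 90%. τ = 10: model SE 0.56, true 0.88, coverage 79%.

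With 3+3 readings in both groups, the step 2 formulas give 92% and 84%, so the imbalance makes matters worse.

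**4. Practices.** A change in a practice that invited and non-invited patients share drops out of the interaction. Simulation with a shared practice change of SD 3 mm Hg gave 95% coverage. Variation w between practices in the exposure-by-period effect does not cancel. It adds w²/8 to the true variance, and the intercept model misses it. With 2+2 readings and τ = 0:

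- w = 1: true SE √(0.5 + 0.125) = 0.79 against 0.71, coverage 92%.
- w = 2: true SE √(0.5 + 0.5) = 1.00 against 0.71, coverage 83%.

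With 50 v 50 patients per practice the ratio of true to model SE is √(1 + w²/4) whatever the number of practices, so recruiting more practices does not remove the problem.

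All of this leaves out covariates and the home/clinic term.

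**The case against.** The strongest reply is that every heterogeneity figure above is assumed. The article gives no SD of change, no between-practice SD of the effect and no reading counts beyond the minimum of four. With no variation in change, or one reading per period, the interval is right. Only one value per day is kept, so same-day home readings collapse. With 2+2 readings and an SD of 5 the loss is two points of coverage. This stands. A reader might infer that the interval is too narrow in any event; the article does not support that.

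Second, a model labelled as repeated measures could carry a within-patient residual covariance that absorbs patient-level change, and such detail is often left to an analysis plan. This stands in part. No such structure is stated or excluded, and it would not cover practice variation in the effect. But the article does list its random effects, and that list does not match a change contrast.

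Third, a reader might infer that any difference between practices in BP change narrows the interval. Shared changes cancel. A reader might also infer that practices implement the system as they please. The article's discretion concerns invitation only ("The choice of which patients receive an invitation is at the discretion of practices"); roll-out is led by the supplier and a national primary care body, with training and support. Effects may still vary, but that sentence does not establish it.

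Fourth, this is a service evaluation. If the target is the average effect in the participating practices, a random practice-by-effect term is not required. This stands, so that part of the fix is conditional on the target.

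**Conclusion.** The point holds in conditional form. The named random effects are intercepts, while the primary contrast is a change with several readings per patient and period. If patients differ in true change and residuals are independent, the interaction's standard error is too small and the 5% level is exceeded. For assumed change SDs of 5 to 10 mm Hg the standard error is too small by a factor of 1.07 to 1.22 with 2+2 readings and 1.18 to 1.53 with 4+4, and the shortfall grows if invited patients contribute many more later readings. Practice variation in the effect adds to this only where inference is meant to reach beyond the participating practices. The direction is firm; the size cannot be fixed from the article. Because individual titration makes differing changes likely and the patient-level remedy is standard, the model should be settled before the analysis.

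**What to change.** Add a patient-level random effect for period, correlated with the patient intercept, or state a within-patient covariance that does the same work.

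State whether inference is to the participating practices or to practices more widely. If more widely, also allow the effect to vary between practices, by one of:

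- a practice-level random exposure-by-period term with small-sample degrees of freedom (Kenward-Roger or Satterthwaite); or
- practice-clustered standard errors with a small-cluster correction, which also serve as the fallback if the richer model does not converge.

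Patient-clustered standard errors would repair the patient part but not the practice part.

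The change to the text is short and needs no new data. It costs wider intervals and less apparent precision. With the 8 to 14 practices planned for, the practice-level variance will be weakly estimated and the fit may be singular, so the fallback should be written down in advance.

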### Subgroups

Analyses and modelling above will be repeated in the following subgroups: (BOX 2)

Male vs. female.Previous history of cardiovascular disease defined here as myocardial infarction or stroke/TIA.People with baseline (clinic) blood pressure ≤ 140/90 mmHg compared to those > 140/90mmHg.Deprivation score (High vs. Low) worst 3 quintiles vs. best 2 quintiles.Ethnicity (white vs. other ethnicity).Geographical Area comparing the three areas where the system has been implemented.

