### Exploratory outcomes

Exploratory outcomes include the evaluation of the impact of the digital intervention on antihypertensive medication use and other cardiovascular preventative treatment (statins, antiplatelets, anticoagulants). Subgroups (see below) will be examined for the comparisons defined in the primary outcome.

Further exploratory outcomes will be addressed using the standalone intervention data. These are detailed below in the Hypertension-Plus outcomes and analysis section.

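### Subgroups are framed as comparisons, but the stated method only repeats the model within each stratum at 5% and names no test of whether the effect differs between strata

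*Protocol article*

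**What the plan says.** The Subgroups section of the protocol article gives the method in one line: "Analyses and modelling above will be repeated in the following subgroups". Six factors follow: sex, previous cardiovascular disease, baseline clinic blood pressure, deprivation, ethnicity and geographical area. Five have two strata (counting cardiovascular disease as yes/no) and area has three, so there are 5 x 2 + 3 = 13 strata.

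Several entries are worded as contrasts. Patients at or below the blood pressure cut-off are to be "compared to those > 140/90mmHg", and the last entry reads "Geographical Area comparing the three areas where the system has been implemented".

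The Statistical analysis section adds "A 5% significance level will be used for all analyses/ tests". The only interaction it names is "interaction terms between the exposure and time period variable".

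The Exploratory outcomes section gives the status of these analyses: "Subgroups (see below) will be examined for the comparisons defined in the primary outcome".

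**The concern.** In this model the exposure-by-period interaction is the effect estimate itself. Refitting the model in women alone tests whether the effect in women is zero. It does not test whether the effect in women differs from the effect in men. The article asks the second question and describes a method for the first.

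When one stratum gives p < 0.05 and the other does not, the contrast wording invites the conclusion that one group benefits and the other does not. With a single common effect and ordinary power, that pattern arises often by chance. The factors include sex, ethnicity, deprivation and area, so a mistaken reading would bear on who is thought to benefit from the service and on equity.

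**Working it through.** **The plan's own figure.** The Sample size section gives 91% power for 800 patients in 8 practices. The inputs are an effect of -3 mm Hg ("Effect size was assumed to be -3 mm Hg"), practice SD 5, patient SD 17, measurement SD 10 and at least 4 readings per patient. The allocation between exposure groups and the before/after split of readings are not given, so the figure cannot be reproduced exactly. Two-sided 5% is assumed, and practice effects are taken to cancel within practice.

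| Layout | SD (mm Hg) | Power |
|---|---|---|
| 400 v 400, mean of 4 readings | sqrt(17² + 10²/4) = 17.72 | 66.8% |
| 400 v 400, change score, 1 + 1 readings | sqrt(2 x 10²) = 14.14 | 85.1% |
| 400 v 400, change score, 2 + 2 readings | sqrt(2 x 10²/2) = 10 | 98.9% |
| 800 v 800, mean of 4 readings | 17.72 | 92.3% |

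Only the last is near 91%, and it is not 800 patients in total. The steps below take 91% as given and use it only to set the scale. They need no assumption about allocation.

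**Overall signal.** z = 1.960 + 1.341 = 3.301.

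**Power within a stratum**, with the same true effect everywhere. A stratum holding share f of the information has z = 3.301 x sqrt(f) and power Φ(z - 1.960).

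- f = 0.5: z = 2.334, power Φ(0.374) = 64.6%.
- f = 0.2: z = 1.476, power Φ(-0.484) = 31.4%.
- f = 0.8: z = 2.952, power Φ(0.992) = 83.9%.

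**Chance that exactly one of two strata is significant**, p1(1 - p2) + p2(1 - p1):

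- 50:50: 2 x 0.646 x 0.354 = 45.7%.
- 30:70 (powers 44.0% and 78.9%): 53.5%.
- 20:80: 0.314 x 0.161 + 0.839 x 0.686 = 62.6%.
- Three equal areas (power 47.8% each), mixed result: 1 - 0.478³ - 0.522³ = 74.9%.

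A simulation of all six factors on the same patients (4,000 runs, 800 v 800, balanced strata, uniform 3 mm Hg effect) gave a mean of 2.9 factors with a mixed result. At least one factor was mixed in 89% of runs.

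**Larger sample.** The article will use as many records as are available. With four times the information, z = 6.601.

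- 50:50: power 99.66% per half, mixed result 0.7%.
- 20:80: powers 83.9% and nearly 100%, mixed result 16%.

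**What a test of difference would deliver.** The overall standard error is 3/3.301 = 0.909 mm Hg. The standard error of the difference between two strata is 0.909 x sqrt(1/f + 1/(1 - f)).

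- 50:50: 0.909 x 2 = 1.818. Power for a 3 mm Hg difference is Φ(3/1.818 - 1.960) = Φ(-0.310) = 37.8%.
- 20:80: 0.909 x 2.5 = 2.272. Power is Φ(1.320 - 1.960) = Φ(-0.640) = 26.1%.
- With a uniform effect, each test has a 5% false-positive rate. For at least one of six, 1 - 0.95⁶ = 26.5% (about 27% in the simulation).

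**The case against.** **The analysis plan may contain the test.** Fitting within strata is a legitimate way to get stratum estimates. Patients in different strata of a factor are different people, so the estimates can be contrasted directly (b1 - b2 over its standard error), which comes close to an interaction test. The 5% sentence would apply equally to such a test, and an article often leaves this detail to a fuller plan. Part of this stands: the article does not exclude a test of difference. But it does state a method, and that method does not answer the comparisons listed beneath it.

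**The subgroups are exploratory.** This stands and limits the severity. It does not make a within-stratum p-value informative about a between-stratum difference.

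**A reader might infer that chance splits will be reported as differential effects.** The article gives no rule for interpreting subgroup results, so the supported statement is that they can be misread.

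**A reader might also multiply up 13 tests.** With no effect anywhere, 1 - 0.95¹³ = 48.7%, but only if the strata are independent. They are overlapping cuts of the same patients, and simulation gives about 35%. That is also a multiplicity problem, which a test of difference reduces but does not remove.

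**The sample is not capped at 800.** This stands. The risk shrinks quickly for equal halves and more slowly for small strata.

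**Conclusion.** The point holds as a mismatch between the question asked and the method stated, in an exploratory analysis. It should be corrected but does not threaten the primary result. At the stated 91% power with one common effect, about 46% of equal two-way splits and about 63% of 20:80 splits would show one significant and one non-significant stratum. At four times the information the figures are about 0.7% and 16%.

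These figures assume two-sided 5% tests, information proportional to stratum share, independent strata within a factor and an identical true effect throughout. They scale from the stated 91%, which could not be reproduced from the inputs given. The mismatch itself does not depend on that figure. Nothing in the article shows that misleading conclusions will in fact be drawn, or that the full analysis plan lacks a test of difference.

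**What to change.** For each factor, fit one model on the full sample with the subgroup x exposure x period term and its lower-order terms (subgroup, subgroup x exposure, subgroup x period), using two degrees of freedom for area. Report the interaction estimate, confidence interval and p-value. Show stratum estimates with confidence intervals as description, and base any claim of differential effect on the interaction only.

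Label the results exploratory and state the two limits derived above: the roughly 26% chance of at least one false positive across six tests, and the low power at the planned size. A non-significant interaction must therefore not be read as equal benefit.

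The cost is a few sentences and the added model terms. No new data are needed. The downside is that at the planned size these tests will seldom settle whether effects differ, so the confidence intervals will carry most of the information.

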**Methods and analyses:**

The study will use a mixed methods approach including both quantitative analysis of anonymised electronic health record data and qualitative analyses of interview and customer support log data. Pseudonymised data will be extracted from electronic health records and outcomes compared between those using the digital intervention and their own historical data, as well as to those not registered to the system. The primary outcome will be difference in systolic blood pressure in the 12 months before and after implementation. A further analysis will utilise self-monitored blood pressure data from the Hypertension-Plus system itself. Semi-structured qualitative interviews will be completed with implementation and clinical leads, staff and patients in six general practices located in two different geographical areas in England. Informed by the non-adoption, abandonment, scale-up, spread, and sustainability (*NASSS*) framework, our analysis will identify the challenges to successful implementation and sustainability of the digital intervention in routine clinical practice and in patients’ homes.

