### Secondary outcomes

Diastolic blood pressure (DBP) in mm Hg, extracted from the electronic healthcare record or the Hypertension-Plus system in the same manner as SBP readings using the same comparison as the primary outcome. A sensitivity analysis considering SBP and DBP in the same way as the primary analysis will include those with uncontrolled BP prior to implementation of the intervention. Controlled BP will be defined as SBP < 140 mm Hg and DBP < 90 mm Hg for clinic readings or SBP < 135 mm Hg and DBP < 85 mm Hg for home readings. Uncontrolled BP will be defined as the presence of any clinic or home SBP or DBP reading at or above these thresholds.

Primary care hypertension workload defined as the number of consultations where hypertension or hypertension monitoring was listed as the primary problem will be compared before and after implementation in a similar way to the BP outcomes.

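### Selecting patients on pre-implementation readings that also count as outcomes builds regression to the mean into the within-stratum before/after change

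*Protocol article*

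**What the plan says.** The abstract states: "The primary outcome will be difference in systolic blood pressure in the 12 months before and after implementation". The Primary outcome section repeats this contrast, "comparing 12 months before and after intervention implementation", and adds a second one: "along with comparison between those on the hypertension register invited to use and not invited to use the intervention". The Statistical analysis section fits a repeated-measures mixed model with exposure, period and their interaction, baseline SBP and DBP among the covariates, and random patient and practice effects.

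Two further analyses reuse this model in selected patients.

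- **Subgroups:** "Analyses and modelling above will be repeated in the following subgroups", one of which is "People with baseline (clinic) blood pressure ≤ 140/90 mmHg compared to those > 140/90mmHg".
- **Secondary outcomes:** "A sensitivity analysis considering SBP and DBP in the same way as the primary analysis will include those with uncontrolled BP prior to implementation". A patient is uncontrolled if any clinic or home reading reaches the threshold.

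On timing, the Statistical analysis section says: "Covariates are defined using the closest available electronic healthcare records data prior to baseline". The Quantitative study section takes the most recent routine data at baseline. Baseline itself is given no date. Nothing says that the classifying reading is left out of the 'before' outcome or comes from an earlier window.

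**The concern.** A single reading above 140 mmHg is, on average, partly above 140 through measurement error. If that reading both admits the patient to the high stratum and counts as a 'before' outcome, the 'before' mean is inflated. The 'after' readings carry no such selected error, so pressure appears to fall. At or below the cut the reverse happens, and pressure appears to rise. The any-high set shows only the fall, as it has no low counterpart.

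This follows from how the sets are defined and would arise even if practices invited patients at random. The before/after change is itself a named outcome, so a spurious within-stratum change could be reported as an effect in people with raised pressure, or as harm in people with controlled pressure.

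**Working it through.** **Inputs (Sample size section).** Mean 148 mmHg; SDs 5 (practice), 17 (patient) and 10 (measurement); effect -3 mmHg; at least 4 readings per patient, with no before/after split given. Assumed here: SBP only, cut at 140, independent errors, true effect zero, and classification on the last reading before implementation.

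**The plan's own figure.** The stated 91% power for 800 patients depends on a group split that the text does not give. The SD of a 4-reading patient mean is √(17² + 10²/4) = 17.72. With 800 users against 800 non-users the two-sided 5% power is 92.3%; with 400 against 400 it is 66.8%. The point below does not depend on this figure.

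**Expected error in the classifying reading.** The SD of one reading is √(25 + 289 + 100) = √414 = 20.35, and z = (140 - 148)/20.35 = -0.393. The normal density at z is 0.369 and the share above the cut is 0.653.

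- Above 140: (100/20.35) × 0.369/0.653 = +2.78 mmHg.
- At or below 140: -(100/20.35) × 0.369/0.347 = -5.23 mmHg.

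**Spurious before/after change.** This is minus the expected error, divided by the number of 'before' readings. The any-high column is simulated.

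| 'Before' readings | >140 | ≤140 | Any reading ≥140 |
|---|---|---|---|
| 1 | -2.8 | +5.2 | -2.8 |
| 2 | -1.4 | +2.6 | -1.1 |
| 4 | -0.7 | +1.3 | -0.4 |

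With the protocol's larger measurement SD of 14 and the other SDs unchanged, the expected errors become +5.09 and -8.99, so the changes in the first row become -5.1 and +9.0 and scale down in the same way.

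**False-positive rate of the before/after test alone.** In 2,000 simulated datasets with 400 invited patients, a nominal 5% test rejected in 91% (high) and 99% (low) with one 'before' reading, 64% and 87% with two, and 34% and 59% with four. The any-high set gave 91%, 46% and 17%.

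**Does the baseline SBP covariate help?** No. A mixed model with patient intercept, period and baseline SBP was fitted to 40 datasets of 800 patients with 2 + 2 readings, leaving out the practice effect. It gave period effects of -1.36 (high), +2.52 (low), -1.07 (any-high) and 0.02 (unselected). Dropping the classifying reading brought the high and low changes to -0.03 and +0.01.

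**Exposure-by-period contrast.** If both groups have the same distribution and the same number of readings, the bias cancels. Otherwise it is the invited change minus the non-invited change. The group means and reading counts below are assumptions.

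| Invited v not invited | >140 | ≤140 |
|---|---|---|
| Means 152 v 144, 2 'before' readings each | -1.14 + 1.66 = +0.52 | 2.97 - 2.28 = +0.69 |
| Means 148 v 138, 2 each | -1.39 + 2.12 = +0.73 | 2.61 - 1.81 = +0.80 |
| Means 152 v 144, 4 v 2 | -0.57 + 1.66 = +1.09 | 1.48 - 2.28 = -0.79 (unrounded inputs) |

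For 148 v 138, the interaction test in the high stratum rejects in 19%, 12% and 8% of datasets with 1, 2 and 4 readings.

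**The case against.** The strongest reply is that the model already contains the exposure-by-period interaction and that the subgroup analyses repeat that model. A reader might infer that the plan is bound to show a benefit in people with raised pressure, and so would misdirect who is offered the system. The documents do not support this. In the interaction, with equal reading counts, the bias has the same sign in both strata and differs between them by only about 0.1 to 0.2 mmHg. In all three scenarios above, the high-stratum bias is positive, which works against the intervention. A false signal in favour of high-pressure patients would need non-invited patients to have more 'before' readings (2 v 4 at means 152 v 144 gives -0.31 and +1.83), and nothing in the protocol suggests that. The remark on better targeting in the Discussion and conclusion is general and not tied to these analyses.

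Other parts of the reply also stand. Baseline is undated; if it meant the start of the 'before' year, the subgroup artefact would largely vanish, although the use of the most recent data points the other way. The uncontrolled set is less open to that defence, because it is defined by status "will include those with uncontrolled BP prior to implementation of the intervention". Size depends on reading counts that the plan does not fix. Home readings pooled into the outcome would dilute a clinic classifier. DBP, the home threshold and the lowest-of-day rule were not modelled.

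What does not fall away is that the before/after change is a named outcome alongside the group comparison. In these sets it is biased.

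**Conclusion.** The point holds for the within-stratum before/after change. Under no effect it is about -2.8/+5.2, -1.4/+2.6 and -0.7/+1.3 mmHg (high/low) with 1, 2 and 4 'before' readings, and about -2.8, -1.1 and -0.4 in the any-high set, against a planned effect of -3. This rests on the protocol's SDs, the SBP-only simplification, and reading baseline as the latest value before implementation.

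The planned interaction removes most of the artefact. A residue of roughly 0.5 to 1 mmHg remains if the groups differ in mean pressure or in number of 'before' readings. A difference in mean is plausible, because The intervention section says that invitees typically have raised pressure; its size is assumed. The selection does not touch the primary analysis in all patients. Severity is minor: the subgroups are listed as exploratory and the uncontrolled set is a sensitivity analysis.

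**What to change.** In these two analyses, take the classifying reading or readings from outside the 'before' outcome data.

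- **Baseline-BP subgroups:** date baseline. Then either classify on a reading taken before the 12-month window opens, or exclude the classifying reading from the outcome.
- **Uncontrolled-BP analysis:** either apply the any-reading rule to readings before the window, or define the set on one specified reading and exclude that reading. Dropping only the last reading while keeping the any-reading rule is not enough, because the other 'before' readings also classify.
- **Reporting:** state that conclusions in these sets rest on the exposure-by-period interaction (by stratum where strata are compared), and that the within-stratum before/after change is not presented as an effect.

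The cost is some wording and, for the earlier window, a longer look-back in the same extract. Precision falls slightly, and patients with a single 'before' reading and no earlier one are lost from these analyses. If the earlier window is used, the classification describes blood pressure status less close to implementation.
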